#### *Recruitment of participants*

Potential participants will be selected from walk-in customers who present at the participating pharmacies seeking help for sleep-related disorders or having symptoms of sleep problems. In both the intervention and control groups, in addition to the usual discussion and service about sleep health, the pharmacist or the pharmacy staff will invite potential participants to join the study. If they show an interest, further discussion will be provided at a private area in the pharmacy prior to obtaining consent. Those who agree to join the study, will be assigned to either intervention or control group participants, based on which pharmacy they attend.

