### Study setting

Four to five community pharmacies in the Brisbane metropolitan area with similar demographic criteria and physical locations will be recruited based on convenience sampling.

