#### *Recruitment of pharmacies*

Contact information of the pharmacies will be obtained from the list of community pharmacies from publically available lists. Community pharmacies which meet the inclusion criteria will be invited to join the study by telephone and informed about the project. If the pharmacist expresses an interest, a research officer will arrange a face-to-face discussion for further explanation of the study and obtain consent. Upon agreement, the pharmacies will be assigned to either intervention or control group, based on convenience sampling.

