### Participants

#### *Sample size*

In similar population-based studies which correlate the results of actigraphy against other measures, i.e. polysomnography and/or sleep diaries, the number of participants recruited varies, ranging from 30 to 450 participants [37-39]. To our knowledge, there is no published research relating to community pharmacy-based interventions utilising actigraphy in sleep health management, therefore no standard reference could be used to determine sample size required for this study. In this study, sample size calculation is based on differences in sleep parameters (sleep onset latency (SOL) and total sleep time (TST)) between actigraphy and sleep diaries [40,41]. Using Power and Sample Size Calculation software version 3.0 2009 (Vanderbilt University), to demonstrate a 20% difference in those sleep parameters between actigraphy versus sleep diary, with 80% power sample and a *p*-value of 0.05, 25 participants are required per study group. To allow for potential dropouts (approximately 10% over 2 weeks), a minimum of 55 participants will be recruited.

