#### *Study outcomes*

The primary outcomes (Table 2) of the study will be evaluated based on these three objectives:

1. To evaluate a community pharmacy-based ‘model of care’ to improve the management of sleep disorders in the community, by comparing:

a. Changes in HRQOL mean scores between and within the intervention care group (ICG) and usual care group (UCG) at baseline and week 2.

b. Changes in sleep scale mean scores – ESS, ISI, MAPI and IRLSSG, between and within the intervention care group (ICG) and usual care group (UCG) at baseline and week 2.

c. Changes in sleep parameter mean scores – sleep efficiency percentage (SE%), total sleep time (TST), number of nocturnal awakenings (NWAK) and sleep onset latency (SOL), between pre– and post–actigraphy sleep report data in the intervention care group (ICG).

2. To evaluate the role of actigraph as an objective sleep assessment instrument to monitor certain sleep disorders, by comparing:

a. Changes in sleep parameter mean scores –total sleep time (TST), number of nocturnal awakenings (NWAK) and sleep onset latency (SOL), between actigraphy and sleep diary at week 1 and week 2 in the intervention care group (ICG).

3. To evaluate the extended role of community pharmacists in managing sleep disorders in the community, by evaluating:

a. Participants’ opinions of sleep health at the end of the study.

b. Willingness and the amount able to pay if such programme is provided as a service in the community pharmacy.

Secondary outcomes (Table 2) to be evaluated are:

1. Participants’ opinions of the community pharmacy and opinions on the use of community pharmacy to seek help for sleep-related disorders.

2. Comparison between groups in sleep-related lifestyle and behaviours at week 2 follow-up.

3. Pharmacist and pharmacy staff opinions regarding the feasibility of the study and the management of sleep disorders in the community pharmacy after participating in the study.

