### Data analysis

Data will be collected from the sleep report generated from the Sleep Consultant™ software, sleep diary, and questionnaires (initial and end of study). Sleep parameters measurement, i.e. sleep efficiency percentage (SE%), total sleep time (TST), sleep onset latency (SOL) and number of nocturnal awakenings (NWAK) of a single participant through either the sleep diary or actigraphy will be averaged from all the data recorded during the 2-week period (recorded as ‘pre’ (week 1) and ‘post’ (week 2) mean scores). There will be no discrimination between weekdays and weekend data. Sleep scale scores to assess sleep health using ESS, ISI, MAPI and IRLSSG survey recorded at baseline and week 2 will be averaged to mean scores for analysis.

Data will be analysed using SPSS 20.0 for windows [53]. This study will consider alpha level of 0.05 for all statistical tests. Using descriptive, paired *t*-test and independent *t*-test – demographic characteristics and sleep scale scores between and within groups will be compared. In the ICG, pairwise differences of sleep parameters mean scores between actigraphy and sleep diary will be calculated using independent *t*-test, and will be used paired-*t*-test in comparing within group, for pre– and post–mean scores (for normally distributed data). To determine correlation between two variables, Pearson’s correlation will be applied. Likert-type questions will be analysed as descriptive analysis.

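### Whole pharmacies (only four or five) form the arms, but the arms are compared by a t-test that treats every participant as independent

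*Protocol article*

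**What the plan says.** - **Number of sites.** Under Study setting the plan states: "Four to five community pharmacies in the Brisbane metropolitan area with similar demographic criteria and physical locations will be recruited based on convenience sampling".
- **Unit of assignment.** Recruitment of pharmacies: after agreement, "the pharmacies will be assigned to either intervention or control group, based on convenience sampling". Recruitment of participants: those who consent "will be assigned to either intervention or control group participants, based on which pharmacy they attend". No pharmacy therefore contributes to both arms.
- **Outcomes compared between arms.** Study outcomes, objective 1, lists as primary the change from baseline to week 2 in quality of life (1a, WHO-5) and in ESS, ISI, MAPI and IRLSSG (1b), intervention against usual care.
- **Test.** Data analysis: by descriptive methods and paired and independent t-tests, "demographic characteristics and sleep scale scores between and within groups will be compared"; "This study will consider alpha level of 0.05 for all statistical tests". Neither this section nor the sample size mentions a pharmacy term, a cluster adjustment or an ICC.
- **Sample size.** 25 per group and at least 55 recruited, chosen "to demonstrate a 20% difference in those sleep parameters between actigraphy versus sleep diary, with 80% power sample".

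**The concern.** An independent t-test estimates its standard error from the scatter between individuals. That is valid only if individuals within an arm are independent. Here the arm is a property of the pharmacy, and the protocol itself gives reasons to expect correlation within a pharmacy. Staff of each intervention pharmacy are trained, read the actigraph reports and give the advice, while usual care is whatever each control pharmacy normally does. Any variation between pharmacies goes straight into the arm difference but is not counted in the t-test's standard error.

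The primary between-group comparisons would then reach significance too often, and one atypical pharmacy could create or hide an apparent effect. This matters because the Discussion paragraph of the Abstract says the study will show efficacy.

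**Working it through.** **Inputs from the protocol.** 4 or 5 pharmacies; 25 per group, so 50 completers; alpha 0.05 (sidedness not stated, two-sided taken); 80% power.

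**Assumptions.** Pharmacies split 2 v 2 (sizes 13, 12 v 13, 12) or 3 v 2 (9, 8, 8 v 13, 12), since the split is not stated. The ICC of the outcome as analysed is 0 to 0.10, since none is given.

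**The plan's own figure.** 25 per group corresponds to a standardised difference of (1.96 + 0.84) × √(2/25) = 0.79, or 0.81 with the t correction. The 20% difference cannot be checked against this because no mean or SD is given. The total reproduces: 50 × 1.1 = 55 (50/0.9 rounds up to 56). The calculation concerns actigraphy against diary, which is measured only in the intervention group, so it gives no power basis for the comparison between arms.

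**Design effect.** DE = 1 + (m − 1) × ICC, with m the size-weighted mean pharmacy size:
- 4 pharmacies: m = (13² + 12² + 13² + 12²)/50 = 626/50 = 12.52
- 5 pharmacies: m = (9² + 8² + 8² + 13² + 12²)/50 = 522/50 = 10.44

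At ICC 0.05: 1 + 11.52 × 0.05 = 1.58 and 1 + 9.44 × 0.05 = 1.47. Effective sample size is 50/DE, that is 31.7 and 34.0. The t-test's standard error is too small by √DE, that is 1.26 and 1.21.

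**True type I error.** Simulated under no effect, 40,000 runs per row, normal outcomes with a random pharmacy effect:

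| Pharmacies | ICC | DE | Effective N | Planned t-test | t-test on pharmacy means |
|---|---|---|---|---|---|
| 4 | 0 | 1.00 | 50.0 | 5.0% | 5.0% |
| 4 | 0.01 | 1.12 | 44.8 | 6.2% | 5.0% |
| 4 | 0.02 | 1.23 | 40.6 | 7.8% | 5.2% |
| 4 | 0.05 | 1.58 | 31.7 | 12.0% | 5.0% |
| 4 | 0.10 | 2.15 | 23.2 | 19.2% | 5.0% |
| 5 | 0 | 1.00 | 50.0 | 4.9% | 4.4% |
| 5 | 0.01 | 1.09 | 45.7 | 6.4% | 4.6% |
| 5 | 0.02 | 1.19 | 42.1 | 7.2% | 4.5% |
| 5 | 0.05 | 1.47 | 34.0 | 10.6% | 4.6% |
| 5 | 0.10 | 1.94 | 25.7 | 16.3% | 4.7% |

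The rows at ICC 0 show that the excess comes from the clustering alone.

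**Degrees of freedom.** The planned test uses 50 − 2 = 48 (critical t 2.01). The design supplies 4 − 2 = 2 or 5 − 2 = 3 (critical t 4.30 or 3.18). This does not depend on the ICC.

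**Power of a valid test.** At a true difference of 0.81 SD, which gives 80% power without clustering, the t-test on pharmacy means has 36% power with 4 pharmacies at ICC 0, 26% at 0.05 and 21% at 0.10. With 5 pharmacies the figures are 46%, 35% and 29%.

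**Would more participants in the same pharmacies help?** With 2 pharmacies per arm, matching the unclustered precision needs n = 25(1 − ICC)/(1 − 25 × ICC/2) per arm. At ICC 0.05 this is 23.75/0.375, about 63. At ICC 0.08 the denominator reaches zero, and no number suffices.

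**The case against.** **Size.** The size of the error rests wholly on an assumed ICC. At 0.01 to 0.02 the true error is only 6-8%, and nothing in the protocol supports 0.10. The outcomes are changes over two weeks, which may remove stable differences between customer populations, and pharmacies are chosen to be alike in demographics and location. This stands as a caution on size. It does not remove the shared staff and advice, and the direction holds for any positive ICC.

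**Split.** The 2 v 2 or 3 v 2 split is inferred. True, but a less even split is worse. With one pharmacy of 25 against three (9, 8, 8), m = (625 + 209)/50 = 16.68 and DE at ICC 0.05 is 1.78, against 1.58 for 2 v 2.

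**Scope.** The section ties the independent t-test to demographics and sleep scales. It names no between-group test for WHO-5 and plans no confidence intervals. So the error is explicit for outcome 1b. It reaches 1a only if WHO-5 is tested the same way, and any interval would inherit the same standard error. The comparisons within the intervention group (1c, 2a) lie outside this point.

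**Remedy.** A mixed model on 4 or 5 pharmacies can estimate the pharmacy variance as zero and fall back on the planned test. In a simulated approximation that allowed for this, the type I error stayed near 3-7% for 2 v 2 and 3 v 2, so the remedy is usable for those splits.

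**Confounding.** Assignment by convenience also confounds pharmacy with arm, and no standard error cures that. This is correct, and it is a further reason for a softer conclusion.

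An analysis plan that is not shown does not answer the point, because the protocol itself names the test.

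**Conclusion.** The concern holds. The stated analysis does not fit the stated assignment. For primary outcome 1b, and for 1a if handled alike, the planned test rejects too often whenever outcomes within a pharmacy are positively correlated. Given 50 completers and a 2 v 2 or 3 v 2 split, the nominal 5% is about 6% at ICC 0.01, 7-8% at 0.02, 11-12% at 0.05 and 16-19% at 0.10. The direction and the 2 or 3 degrees of freedom follow from the design. The percentages depend on an ICC that the protocol does not give. A valid analysis of so few pharmacies cannot carry a confirmatory claim of efficacy, and the planned t-test conceals this.

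**What to change.** 1. State in Study design and Data analysis that the pharmacy is the unit of assignment, and give the number of pharmacies in each arm.
2. Replace the independent t-test for the between-group outcomes, and name the test for WHO-5. The simplest choice is to compare baseline-adjusted pharmacy means by a t-test on (number of pharmacies − 2) degrees of freedom. The alternative is a linear mixed model on participants with baseline as covariate, a random pharmacy effect and Satterthwaite degrees of freedom (SPSS MIXED).
3. Report the estimated ICC, noting that 4 or 5 pharmacies estimate it poorly, and show the results by pharmacy.
4. Present the between-group results as estimates with the wider intervals, say that pharmacies were not randomised, and soften the efficacy wording in the Abstract.
5. If recruitment still allows it, add pharmacies before adding participants to existing ones.

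Items 1 to 4 change only the analysis and its wording. Their price is wider intervals, low power (about 21-46% at 0.81 SD over ICC 0.10 to 0) and a weaker conclusion. Only item 5 recovers power, and it needs more sites, training and devices.

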#### *Intervention participants - intervention care group (ICG)*

At baseline, study eligibility (Table 1) will be checked and inform consent will be obtained before the recruited participants complete the ‘Initial Pharmacy Visit’ questionnaires. Sleep-hygiene advice will also be provided to the participants. Due to the pragmatic nature of the study, eligibility criteria are not restricted to specific sleep disorders.

**Table 1 T1:** Participant eligibility criteria

**Eligibility criteria**	
**Inclusion**	**Exclusion**
• Aged ≥ 18 years old	• Aged < 18 years old
• Attend a participating pharmacy as a ‘walk-in customer’ seeking help for sleep-related disorders or having symptoms of sleep disorders.	• Not able to speak, read and write in English, or not fluent in English and cannot arrange for a translator themselves or a translator is not available.
	• Unable to complete the screening (in the pharmacist’s opinion).
	• Refuse to give consent.
	• Pregnant.
	• Currently under treatment with continuous positive airway pressure (CPAP)

The actigraph is a useful device for monitoring sleep-related disorders, but literature suggests that it should be used in conjunction with other parameters, such as sleep diaries [31,42] as both may complement each other by providing objective and subjective data, respectively. Therefore, participants will be provided with an intervention package, which includes:

1. An actigraph (SBV2 Readiband™) to be worn 24-hours a day for seven days before participants revisit the pharmacy for their first follow-up, and then for a further seven days after the first follow-up before returning to the pharmacy for final assessment.

2. A sleep diary [43] to self-record 14 days of bedtime, wake time, time to fall asleep, number of nocturnal awakenings and total sleep time, plus information related to sleep-hygiene, lifestyle and other factors that may interrupt sleep.

3. Educational information about sleep disorders, sleep health management, sleep hygiene and healthy lifestyle to improve sleep (via access link to a website: http://sleepproblemandyou.wordpress.com/ which is developed specifically for this study). The web address will be provided to each participants.

One complete study duration for a participant in the intervention group is two weeks with follow-ups at two time points; week 1 (day 8) and week 2 (day 15). At both time points, pharmacy staff will analyse the data downloaded from the actigraph using Sleep Consultant™ software to generate an on-the-spot individualise report of sleep/wake patterns and they will also assess the self-report information from the sleep diary.

##### 

**Follow-up 1** The participants will receive sleep advice and possible solutions focusing on behavioural strategies such as sleep hygiene, change of lifestyle, daily alcohol and caffeinated drinks consumption and activities before going to sleep, based on data gained from both parameters. Any requests for sleep medicine (‘Pharmacist only medicine’ or ‘Pharmacy medicine’) will follow the pharmacy’s standard practice. After this session, the participants will continue to wear the actigraph plus complete the sleep diary for another seven days.

##### 

**Follow-up 2 / end of study** Participants’ first (pre) and second (post) individual sleep reports will be compared to assess any particular improvement in their sleep condition after receiving sleep advice and possible solution during the first follow-up. Participants will also complete the ‘End of Study’ questionnaires. In certain circumstances (see the ‘Protocol to refer participant to a general practitioner’ subsection), pharmacists can recommend a GP referral for further examination.

##### 

**Protocol to refer participant to a general practitioner (GP) at the end of study** In these circumstances: (1) if the sleep efficiency percentage (SE%) is below 85% at the end of study (normal SE% for adult if measure using actigraphy is 85% and above) [41,44], and (2) if analysis of the data collected appears to indicate that he/she may be at risk of having/developing sleep-related problems and has reported symptoms such as:

• choking or suffocating during sleep

• stopping breathing when sleep

• snoring during sleep

• excessive daytime sleepiness

• difficulty falling asleep at night

• having problems waking up in the morning

• falling asleep too early at night

• waking up too early at night

• fatigue and having difficulty concentrating on daily tasks

• experiencing unpleasant sensations with an urge to move their limbs

Above symptoms may be indicative of another sleep disorders, specifically OSA, narcolepsy, a circadian rhythm disorder, restless legs syndromes or a primary mood disorder.

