### Pharmacies

#### *Pharmacy eligibility criteria*

Community pharmacies that meet the following criteria are eligible to participate as a study site:

• Pharmacies that have high daily ‘walk-in customer’ turnover i.e. 100 to 300 customers per day for any ‘Pharmacist only medicine’, ‘Pharmacy medicine’, over-the-counter medicines including herbal supplements.

Additional criteria for the ‘Intervention care group’ pharmacies:

• Agree to install a software application (Sleep Consultant™ by Fatigue Science) which enables data to be downloaded from the actigraph to generate an individual sleep report for the participants.

• Have a private counselling area within the pharmacy where one-to-one consultations with customers will be separated from the common pharmacy counter.

• Able to follow-up participants for 2 weeks from baseline.

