#### *Control participants - usual care group (UCG)*

The usual care group (UCG) participants will receive standard or usual care for sleep disorders based on the usual practice in the community pharmacy. Australian community pharmacies usually follow the Pharmaceutical Society of Australia’s recommended practice [45], which includes supplying ‘Pharmacy medicine’, ‘Pharmacist only medicine’, complementary medicine or other over-the-counter (OTC) medicines for sleep-related disorders, if indicated. At baseline, follow the same protocol as in the intervention group, study eligibility (Table 1) will be checked and inform consent will be obtained before the participants complete the ‘Initial Pharmacy Visit’ questionnaires. Baseline demographic and assessments will be completed for comparisons with the ICG participants. The UCG participants will be followed-up after two weeks by the study researcher via email or mail to complete the ‘End of Study’ questionnaires.

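### Week-2 questionnaires in the ICG are tied to returning for the final intervention visit, while the UCG is reached by email or mail, so loss may differ by arm and be related to adherence.

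*Protocol article*

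**What the plan says.** **ICG.** The section on intervention participants asks for 24-hour actigraph wear for seven days up to a first pharmacy follow-up, then for a second week "before returning to the pharmacy for final assessment". A sleep diary runs over the same 14 days, and the follow-ups fall on days 8 and 15. The paragraph on Follow-up 2 / end of study compares the two sleep reports and adds: "Participants will also complete the ‘End of Study’ questionnaires". Among the extra criteria for intervention pharmacies only, Pharmacy eligibility criteria lists "Able to follow-up participants for 2 weeks from baseline", so the pharmacy is the follow-up route in this arm.

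**UCG.** The section on control participants says: "The UCG participants will be followed-up after two weeks by the study researcher via email or mail", to complete the same questionnaires. No pharmacy visit after baseline is described.

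**Use of the answers.** Under Study outcomes, 1a and 1b compare change in WHO-5 and in ESS, ISI, MAPI and IRLSSG between and within the arms. Objective 3 uses opinions of sleep health (3a) and "Willingness and the amount able to pay if such programme is provided as a service in the community pharmacy" (3b). Both come from the close-out survey, which Table 2 gives to both arms at week 2.

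**Loss.** Sample size provides for it by number alone: "To allow for potential dropouts (approximately 10% over 2 weeks), a minimum of 55 participants will be recruited".

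**The concern.** Two collection routes are written down, one per arm. In the ICG, the described moment for week-2 answers is the visit that closes the intervention, after two weeks of device, diary and an interim visit. In the UCG it is a form from the researcher that does not depend on any programme. Someone who loses interest in the programme and does not come on day 15 has no other route described for giving answers.

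If such people are also those whose sleep did not improve, the ICG means in 1a and 1b describe people who stayed with the programme, and they look better than the mean of everyone enrolled in that arm. The ICG answers to 3a and 3b are exposed in the same way: they are meant to show whether the service is valued, and people who reject it are the least likely to attend its last visit. Recruiting 55 rather than 50 restores the count but not the make-up of those who answer. No later analysis can recover answers that were not collected.

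The actigraphy and diary outcomes (1c, 2a) exist only in the ICG and lie outside this between-arm concern.

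**Working it through.** **The plan's own figure.** 25 per group × 2 = 50. Adding 10% gives 50 × 1.10 = 55, as stated. Dividing by the retained share gives 50 / 0.90 = 55.6, so 56. The difference is trivial. The 10% is not split by arm.

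**Inputs for the bias.** The documents give the 10% loss and 25 per group. They give no loss by arm and no outcome gap between those lost and those who return. These are assumed:
- q = share of the ICG with no week-2 answers: 10% (plan), 20%, 30%.
- g = how much worse those lost fare than those who return, in SD of the outcome compared: 0.25, 0.5, 1.0.
- Loss in the UCG: none (assumed, to isolate the ICG effect).

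**Formula.** Let C be the mean among ICG returners. The mean of the whole arm is (1 − q)·C + q·(C − g) = C − q·g. The observed mean is C, so the bias is q × g. The false-positive rate under no true effect uses a normal approximation at two-sided 0.05, with 25 analysed per arm, so the standard error is √(2/25) = 0.283 SD. Participants are treated as independent.

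| q | g = 0.25 | g = 0.5 | g = 1.0 |
|---|---|---|---|
| 10% | 0.025 SD; 5.1% | 0.05 SD; 5.4% | 0.10 SD; 6.4% |
| 20% | 0.05 SD; 5.4% | 0.10 SD; 6.4% | 0.20 SD; 10.9% |
| 30% | 0.075 SD; 5.8% | 0.15 SD; 8.3% | 0.30 SD; 18.5% |

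For scale, 25 per arm detects a difference of about 0.81 SD at 80% power (two-sided t-test).

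**With UCG loss.** The net bias is q(ICG) × g(ICG) − q(UCG) × g(UCG). With 10% lost and a 0.5 SD gap in both arms it is 0.05 − 0.05 = 0. With 20% lost in the UCG instead it is 0.05 − 0.10 = −0.05 SD, now against the intervention. If UCG non-responders fare better than responders, g(UCG) is negative and the two terms add.

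**Willingness to pay in the ICG.** Suppose 80% of those who return and 20% of those who do not would pay (assumed). At 10% lost, the share in the whole arm is 0.9 × 80% + 0.1 × 20% = 74%. At 20% lost it is 0.8 × 80% + 0.2 × 20% = 68%. The reported figure is 80% in both cases.

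**The case against.** The article does not say that ICG non-attenders go uncontacted, nor that stopping the device ends outcome collection. Study measurements says week-2 follow-up takes place in both groups, and a procedure for chasing missed visits is often left to a full protocol. This stands: the absence of a chasing procedure is not the point. The point is that two different routes are stated, and the ICG route is the intervention visit itself.

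A reader might infer more, and the text does not support it:
- **That week-2 ICG answers come only from those who return.** This follows from a single described route and is nowhere stated as a rule. Someone who takes the band off or misses day 8 can still attend on day 15.
- **That every control is pursued.** One contact by email or mail is described, with no reminders.
- **That people disappear from one arm only.** Controls can leave a form unanswered, perhaps more readily than participants miss a visit at which they receive their own sleep report.
- **That those who stop the programme are classed as dropouts.** Sample size does not define the term.
- **That objective 3 rests on ICG finishers alone.** The close-out survey goes to both arms, so only the ICG part of 3a and 3b is exposed.

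It is also fair to say that the effect is small at the planned loss. The 0.30 SD figure needs three times that loss, a full 1 SD gap and no loss among controls.

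**Conclusion.** The concern holds in a limited form. As described, week-2 response in the ICG is linked to returning for an intervention visit, and in the UCG it is not. Differential, adherence-related loss is therefore possible in outcomes 1a and 1b and in the ICG answers to 3a and 3b. At the planned 10% loss, with an assumed gap of 0.5 to 1 SD and no UCG loss, the bias is 0.05 to 0.10 SD and the false-positive rate 5.4% to 6.4%. It becomes material only if ICG loss is well above plan: 0.10 to 0.30 SD at an assumed 20% to 30% loss with the same gaps. A claim that the comparison is bound to favour the intervention is not supported, because UCG non-response may offset, reverse or add to the effect. The change is worth making because it costs little and must be in place before the answers are lost.

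**What to change.** In the ICG section and the Follow-up 2 paragraph, state that stopping the actigraph, the diary or the visits does not end follow-up. Have the researcher send the End of Study questionnaires, including the close-out survey, at two weeks by the UCG's email or mail route to every ICG participant who does not attend Follow-up 2. Alternatively, to keep the routes alike, send them this way to all participants in both arms. Count these answers in the ICG for 1a, 1b, 3a and 3b, and report week-2 questionnaire return by arm.

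**Cost.** The change needs a few sentences and a few mailings. With about 55 / 2 = 27.5 participants in the ICG, 10% to 30% non-attendance means roughly 3 to 8 extra contacts. Mailing everyone adds about 28. If only non-attenders are mailed, the ICG will hold a mix of pharmacy and mailed forms; the same route for all avoids that. Some forms will still not come back.
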